###### Transcranial magnetic stimulation

TMS will be used as a non-invasive approach to evaluate quantitatively the excitability of the corticospinal motor pathway. Single-pulse TMS (Magstim rTMS, Magstim Company Ltd, UK) will be applied using a figure-8 coil (90 mm outer diameter) over the arm area of the contralateral primary motor cortex while the subject will be comfortably seated in their wheelchair or the Magstim TMS chair. The optimal position (hotspot) for evoking MEPs preferentially in the bicep brachii muscle will be determined for both arms. The hotspot is defined as the scalp location that elicited MEPs of the largest amplitude in the bicep brachii muscle.^49–51^ This location is typically found lateral and anterior to the vertex, near the hand area of the primary motor cortex. The hotspot will be visualised on a computer through a neuronavigation system (Brainsight system; Rogue Research, Canada), which will ensure that the stimulation coil is maintained in the same position across all three assessment time points. The coil held by an experimenter will be positioned at a 45-degree angle relative to the midline.^52^ The active motor threshold (aMT) will be determined as the stimulus intensity at which 5 of 10 stimuli evoke a MEP larger than 100 μV of amplitude in the slightly contracted bicep brachii.^53^ Stimulus intensity will then be set at 120% of aMT, and 10 pulses will be delivered to characterise latency and amplitude of MEPs. A similar procedure will be performed to obtain the resting motor threshold (rMT) and characterise MEP during rest, where TMS will be applied without any contraction of the bicep brachii. The outcome measures will be the aMT and rMT for the targeted muscle. The latency, area and duration of the silent period (if present) will be also determined.

###### Somatosensory-evoked potentials

Participants will be comfortably seated in a chair or in their wheelchair. For each arm, the median nerve will be briefly stimulated using an electrode placed proximal to the wrist. This stimulation will be used to elicit SSEPs for each upper limb.^54–59^ A 32-channel EEG cap^60^ (Brain Vision Recorder 2.0, Brain Products GmbH, Gilching, Germany), with electrodes arranged according to the international 10-20 system,^61^ will be placed on the participant’s head to record cortical neuronal activity during the stimulation. During the 10-min EEG recording, median nerve stimulation will be delivered at a 3 Hz frequency for a total of 1800 stimuli. Each stimulus will last 0.001 s, with an inter-stimulus interval of 0.333 s. This repetitive stimulation will be delivered at an intensity corresponding to 5% of the maximal muscle response amplitude of the abductor pollicis brevis for each hand. The EEG will be recorded with the Fz electrode as the reference, as it is commonly used in the literature for upper limb stimulation.^57
58
62
63^ The sampling rate will be 5000 Hz.

In the post-recording phase, the raw EEG will be processed to generate the SSEPs using the BrainVision Analyzer 2.0 (Brain Products GmbH, Gilching, Germany), including filtering and averaging.^54
58
64^ Emphasis will be placed on the signals from the region of interest channels, C3/4 and their neighbouring electrodes (Cz, C1/2, Fcz, Cp3/4). The expected SSEPs are the N20 and the P25 that are consistently reported in SSEP studies done in SCI population.^65–68^ The N20 is a negative-going deflection of the baseline that peaks approximately 20 ms after the onset of the electrical stimulus at the median nerve.^67^ The P25, on the other hand, is a positive-going deflection that peaks around 25 ms from the onset of the stimulation, usually following the N20. In addition to the two primary early-latency SSEPs, the P50 and N70 components will also be explored.^69
70^ The P50 is a positive deflection peaking approximately around 50 ms following the median nerve stimulation onset, while the N70 is a subsequent negative deflection that peaks around 70 ms after stimulus onset. The outcome measures will be the absence or presence of SSEP. If present, the amplitude and the latency of the response will be measured to assess the excitability of the ascending somatosensory pathways.

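### The nominal 3 Hz SSEP stimulation rate divides 60 Hz mains exactly, so averaging is a weak defence against mains pickup; a non-commensurate or jittered interval would remove this at almost no cost

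*Protocol article*

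**What the plan says.** All the settings are in the section Somatosensory-evoked potentials of the protocol article. The recording length is given by "During the 10-min EEG recording", and within it "median nerve stimulation will be delivered at a 3 Hz frequency for a total of 1800 stimuli". The next sentence adds: "Each stimulus will last 0.001 s, with an inter-stimulus interval of 0.333 s". For the EEG, "The sampling rate will be 5000 Hz". Post-processing is described as "including filtering and averaging", without filter type or cut-offs.

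The main components are the N20, which "peaks approximately 20 ms after the onset of the electrical stimulus at the median nerve", and the P25, a "positive-going deflection that peaks around 25 ms from the onset of the stimulation". On how the result is scored: "The outcome measures will be the absence or presence of SSEP"; where a response is present, its amplitude and latency are also measured.

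Table 2 lists SSEPs among the secondary neurophysiological measures at T1, T2 and T3. The site is in Québec (Design and setting). The section does not mention mains frequency, interval jitter or line-noise handling.

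**The concern.** Averaging recovers an evoked potential because activity that is not time-locked to the stimulus cancels over sweeps. Mains pickup normally cancels too, because each stimulus falls at a different point of the mains cycle. If the interval between stimuli is a whole number of mains cycles, each stimulus falls at nearly the same point, and the pickup adds up as a response would.

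A rate of 3 Hz meets that condition on 60 Hz mains, and also for the 120 and 180 Hz harmonics (40 and 60 cycles per stimulus). A coherent residue at 60 Hz can shift the measured N20 and P25 and can blur the decision whether a response is present. Pickup may well differ from one session to the next, so the error would enter the comparison of T1, T2 and T3 in a trial of 40 participants. The rate, count, duration and interval are all stated, so this concerns a chosen setting and not an omitted detail.

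**Working it through.** **Inputs from the protocol article (Somatosensory-evoked potentials):** 3 Hz, 1800 stimuli, 10 min = 600 s, pulse 0.001 s, interval 0.333 s, N20 at about 20 ms, P25 at about 25 ms.

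**Assumptions:** mains at 60 Hz; for the wander scenario, a mains frequency that drifts around 60 Hz with SD 0.01-0.02 Hz. Everything below is before any filter.

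**1. The article's own count.** 3 × 600 = 1800, which reproduces exactly. With a literal 0.333 s from onset to onset, 600/0.333 = 1802. With a 0.333 s gap plus the 0.001 s pulse, 600/0.334 = 1796. The stated count fits 3 Hz exactly and the other two readings to within a few stimuli, so it does not settle which interval would be programmed.

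**2. Mains cycles per stimulus** (60 × interval):
- 1/3 s: 20.00
- 0.333 s: 19.98
- 0.334 s: 20.04
- 1/3.1 = 0.3226 s: 19.35

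**3. Share of mains amplitude left after averaging.** For N = 1800 sweeps, mains frequency f and interval s, the residual is |(1/N) Σ exp(2πi·f·s·k)|, k = 0 to N−1.

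| Interval | Mains | Residual |
|---|---|---|
| 1/3 s | exactly 60 Hz | 100% |
| 1/3 s | constant offset 0.0005 Hz | 86% |
| 1/3 s | constant offset 0.001 Hz | 50% |
| 1/3 s | constant offset 0.002 Hz | 16% |
| 0.333 s | exactly 60 Hz | at most 0.9% (1700-1800 sweeps) |
| 0.334 s | exactly 60 Hz | at most 0.5% (1700-1800 sweeps) |
| 0.3226 s (3.1 Hz) | exactly 60 Hz | under 0.1% |

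For larger constant offsets Δ at 1/3 s, the residual is bounded by 1/(π·Δ·600): 10.6% at 0.005 Hz, 5.3% at 0.01 Hz, 2.7% at 0.02 Hz. Unrelated noise falls to 1/√1800 = 2.4%.

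**4. Wandering mains, simulated** (Ornstein-Uhlenbeck frequency). At 1/3 s the median residual is 22% and 19% for SD 0.01 Hz (correlation time 60 and 300 s), and 16% and 14% for SD 0.02 Hz; repeat runs reach down to 13%. A correlation time of 10 s gives 28% and 17%. Under the same wander, a literal 0.333 s leaves about 1% (0.6-2% over these settings), 0.334 s about 0.3-0.5%, and 3.1 Hz less than 0.1%.

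**5. Effect on the N20-P25 difference.** A 60 Hz sine of amplitude A changes by at most 2A·sin(π × 60 × 0.005) = 1.62A over 5 ms, at the worst phase. The article gives no pickup amplitude. For an assumed 0.5 μV, a 13-22% residual is 0.065-0.11 μV and moves the difference by at most 0.11-0.18 μV. For an assumed 5 μV, the figures are 0.65-1.1 μV and at most 1.05-1.78 μV.

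**The case against.** **Pickup does not simply survive averaging.** A reader might infer from 60/3 = 20 that mains passes through 1800 averages untouched. That needs mains and stimulator clock to agree to well under 0.001 Hz for ten minutes. With the assumed wander, averaging removes about 78-87% of the amplitude. This stands: the weakness is partial retention, still well above the 2.4% for unrelated noise.

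**The problem holds under one reading of the interval.** Programmed literally, 0.333 s or 0.334 s nearly removes it. This stands too. The 0.333 s figure is most naturally a rounding of 1/3 s, so it would be wrong to call the two sentences a contradiction. But two settings that look interchangeable act differently on the averaged signal, and the article does not say which one the operator enters.

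**Filtering is planned.** All residuals above are before filtering. Filter settings can properly sit in the full protocol or the procedure manual that the article announces, so their absence is no fault. They do leave the true effect unquantified.

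**The waveform does not closely match mains.** A reader might say that residual mains mimics the N20-P25 pair. The mains period is 16.7 ms, whereas a 5 ms peak-to-peak interval implies a cycle of about 10 ms. The periods are not close. The residue can distort the measurement, but the documents do not show that it would create or hide responses.

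**The consequence is limited.** SSEPs are secondary measures under an exploratory objective; the primary outcome is the upper extremity motor score. Both arms are recorded in the same way at the same visits, and nothing suggests that pickup depends on allocation.

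**Conclusion.** The concern holds in a limited form. At a true 1/3 s interval on 60 Hz mains, the stated rate is a poor acquisition setting: the median residual under the assumed wander is roughly 5 to 9 times the 2.4% for unrelated noise (13/2.4 = 5.4; 22/2.4 = 9.2), and a rate of 3.1 Hz removes the problem. This rests on two assumptions that the documents do not confirm, the 60 Hz mains and the size of its wander, and on the interval being programmed as 1/3 s.

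The effect in microvolts is unknown. The harm to expect is extra visit-to-visit noise in SSEP presence, amplitude and latency. A reader might go further and infer a biased comparison between arms or false recovery of responses; the documents support neither. This is a cheap technical improvement to a secondary measure and does not touch the primary analysis.

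**What to change.** In the section Somatosensory-evoked potentials, replace the paired rate and rounded interval by one onset-to-onset interval, given to enough decimals to be programmed without ambiguity and well away from any multiple of 1/60 s. For example, 3.1 Hz is an interval of 0.3226 s, and 1800 stimuli take 1800/3.1 = 581 s, about 9.7 minutes. Alternatively, jitter the interval at random and evenly over one or more whole mains cycles (16.7 ms each); mains then averages like unrelated noise, to about 2.4%. Use the same setting at T1, T2 and T3 for every participant.

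The cost is one stimulator setting and one sentence. Stimulus count and staffing stay the same, and recording time is about 20 s shorter. The downside is a slight departure from the round 3 Hz rate. It should be made before the first participant is recorded, since a change during the trial would itself add a difference between visits.

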### Intervention

#### Usual care

Usual rehabilitation care is delivered by a multidisciplinary team and focuses on maximising functional independence and reintegration into daily life. Typically, physical and occupational therapy sessions are delivered 4 times per week for 45 min per discipline, in addition to self-directed exercises. Occupational therapy sessions focus on developing physical capacity, self-care skills and mobility, whereas physical therapy sessions comprise strength-based exercises, balance and mobility exercises. The key principles of ABT are integrated in usual care. The possibility to participate in 1 hour of self-directed exercises is offered in a therapeutic gym equipped with a stationary bicycle and strengthening equipment. Individuals with SCI are also followed by a medical and psychosocial team comprised of a general practitioner, a physiatrist, a psychologist, a social worker and a nutritionist. Educational workshops are additionally offered to help participants better understand and manage their condition, promoting a holistic approach to rehabilitation. All participants will receive usual care in addition to the intervention, as per group allocation.

#### Training

ABT: Participants will receive 45 min sessions of active ABT+tSCS or sham, 3 times per week for 6–8 weeks, for a total of 20 sessions. The content of the ABT was developed using a participatory research approach with four occupational therapists and one physical therapist from the spinal cord programme at IRGLM, one patient-partner with C3-C4 tetraplegia and a caregiver.^71^ The ABT comprised five key sections: cardiovascular training, weight bearing and stretching and visually guided motor control training,^72
73^ strengthening and task-oriented training. The sequence of the ABT sections was designed to optimise neuromuscular activation, participant engagement and transfer of skills to real-life activities. Between sections, short breaks will be allowed to maximise engaged time-on-task. Time in active treatment will be recorded using a stopwatch to meet the 45 min target. Transitions between activities and rest periods during the task of more than 2 min will not be counted towards the total active time. Time targets are set for each ABT section, with a minimal duration for each ABT section (see table 3 for an overview of the time and content for each section). For participants with limited endurance, the minimal duration for each section will be offered in the first week and then will be progressively increased to meet the target duration by the end of week 3. The ABT protocol will be administered by a trained interventionist with a clinical background (physical or occupational therapy). Each participant will be paired with an interventionist to deliver the ABT protocol and a graduate student or research associate to apply the spinal cord stimulation (sham or active tSCS). The ABT protocol will be progressed to the needs of each participant. A collaborative approach will be used to select each activity. Participants will be encouraged to use their personal assistive devices (eg, universal cuff, adapted utensils) during task-oriented training.

**Table 3 T3:** Section and time targets of the activity-based training session

Section	Target duration	Minimal duration	Key elements
Cardiovascular training	2 min	2 min	Modified jumping rope, Ergo-cycle (assisted or independent) or Vita-glide Moderate intensity (target of 4–5/10 on the modified Borg Perceived Exertion Scale)
Weight bearing and stretching	6 min	5 min	Weight-bearing on the forearm or the hand Stretches of the shoulder (flexion/extension, abduction, internal/external rotation), elbow (flexion/extension), wrist (flexion/extension) and fingers (flexion/extension, palm stretching, opposition)
Visually guided motor control training	6 min	3 min	Participants are instructed to make a cursor follow a series of target lines on a computer screen by performing voluntary flexion and extension movement within available range of motion guided by real-time joint angle feedback using an electrogoniometer (shoulder, elbow, wrist or hand)
Strengthening	8 min	6 min	Concentric, eccentric or isometric contractions of targeted group muscles (shoulder flexor or abductors, scapula, biceps, triceps, wrist extensors, pinches)
Task-oriented training	23 min	18 min	35 different tasks classified into seven categories: reaching, grasping, grasping with rotation, pinch, pinch with rotation, in-hand manipulation and finger isolation

#### Training: transcutaneous spinal cord stimulation

*Skin preparation and electrode configuration:* Prior to stimulation, the skin over the stimulated area will be cleaned with isopropyl alcohol. Once dried, the area will be prepared with Tape Skin Prep Electrode (Red Dot Trace Prep, 3M Canada) to reduce skin-electrode impedance. A single or two self-adhesive cathode electrodes (Dura-Stick plus double wire or ROHVEMJ transcutaneous electrical nerve stimulation electrodes) will be placed either along the midline or paravertebral region (still covering the midline), depending on potential significant asymmetries in the motor abilities of each participant. The electrodes will span the C4 to T1 vertebral levels at first to try and facilitate activity from any motoneuronal pool. In participants with better recovery, the electrode will only cover more caudal parts depending on what muscle needs to be facilitated. A pair of reference anodal self-adhesive electrodes will be placed bilaterally on the external part of the clavicular regions. All electrodes will be secured with elastic adhesive bandages (Tensoplast, BSN Medical-Essity, Sweden) to ensure optimal skin contact.

#### Experimental group

*Stimulation protocol:* Participants will receive tSCS throughout the ABT sessions. Stimulation will be delivered using a NeuroTrac Myoplus4 Pro (Verity Medical Ltd., UK). This stimulator provides the necessary range of intensity and frequency required, although the pulse duration is limited to 400 microseconds. Preliminary testing on able-bodied participants as well as SCI participants demonstrated that it could facilitate voluntary movement. Individualised tSCS parameters (30–80 Hz, 0–90 mA, biphasic 400μs pulse square) will be used to facilitate upper limb movement.

*Identification of stimulation parameters:* The effective stimulation parameters, frequency and intensity, will be determined prior to the first training session based on their ability to facilitate, if possible, a predefined voluntary movement. Facilitation is defined as an increased ease of movement reported by the patient accompanied by enhanced muscle activity, greater joint range of motion and/or improved motor control. This initial process will be guided by objective measurements using surface EMG, an electronic goniometer or visualisation of muscle twitch. First, electrode placement will be adjusted to ensure appropriate coverage of the upper limb myotomes targeted. Then, three frequencies will be tested based on what has been reported as efficient frequencies in the literature: 30 Hz, 50 Hz and 80 Hz.^21
74^ For each frequency, effective intensity will be defined as the lowest stimulation amplitude that reliably elicits facilitation without inducing pain or strong contractions that could hinder active training. Position and frequency will be kept constant throughout the training session but since physiological state and tolerance may vary from session to session, stimulation intensity will be reassessed at the beginning of each session. Reassessment will rely on visual observation to confirm the presence of facilitation. If the intensity required to elicit facilitation initially exceeds the participant’s tolerance, amplitude will gradually be increased during the session. If facilitation cannot be achieved at a tolerable intensity, it will be reported in the treatment notes and considered for interpretation of the effects. For each session, we will systematically document the muscles showing facilitation or visible twitches, the stimulation frequency and effective intensity used, the participant’s reported tolerance and any within-session parameter adjustments.

#### Control group

Participants assigned to the control group will follow the same procedure administered for participants in the experimental group for the ABT, except for the tSCS that will be delivered at sub-therapeutic intensity (2–3 mA). This level of stimulation will activate cutaneous afferents but remains below the threshold required to activate motor or sensory afferents.

### Data management and analysis

All study data will be collected, stored and managed in accordance with applicable ethical and regulatory standards to ensure participant confidentiality. Written informed consent forms will be kept in a secure, locked location within the clinical research facility. Data will be accessible only to authorised members of the research team. Questionnaire responses and results sheets will be stored as either paper or electronic records in REDCap. Hard-copy documents will be maintained in locked cabinets within the research facility, while electronic data will be anonymised and stored on password-protected computers in a secure environment. In compliance with the research centre’s data retention policy, all study data will be securely archived 7 years following study completion.

### Statistical analysis

The Shapiro-Wilk test will be used to assess the distribution of continuous variables for both demographic and outcome measures. Normally distributed continuous data will be summarised as mean with SD, while non-normally distributed data will be presented as median with IQR. Categorical variables will be reported as frequencies and percentages. Specific injury-related characteristics (eg, level and severity of injury) will be considered for exploratory subgroup analyses. To evaluate changes over time and differences between groups, a linear mixed-effects model will be fitted with fixed effects for group (ABT+tSCS and ABT+sham), time (pre, post and 1-month follow-up) and the group×time interaction and a random effect for participant to account for within-subject correlations across repeated measurements. The primary effect of interest will be the group×time interaction, which will be used to determine whether changes over time differ between groups. Where a significant group×time interaction is observed, estimated marginal means will be compared using post hoc pairwise contrasts with appropriate adjustment for multiple comparisons. Missing data will be handled using an intention-to-treat approach, with all available observations included in the mixed-effects model. If warranted, sensitivity analyses using multiple imputation may also be conducted to assess the robustness of the findings. The threshold for statistical significance will be set at p<0.05 for all analyses.

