### Trial objectives

The overall objective of this RCT is to determine the effect of a supplemental intervention combining cervical tSCS+ABT on upper limb motor recovery, compared with supplemental ABT alone, in individuals with subacute cervical SCI undergoing standard in-patient rehabilitation. Participants will receive 20 intervention sessions, administered three times per week over 6–8 weeks, in addition to their usual care. Assessments will be conducted at baseline (pre-intervention), immediately post-intervention and at a 1-month follow-up. The primary outcome measure is the Upper Extremity Motor Score (UEMS) from the International Standards for Neurological Classification of Spinal Cord Injury (ISNCSCI), an established indicator of upper limb motor impairments.

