### Secondary objectives

To determine the safety of the intervention (ie, minor and major adverse events (AEs)).To determine changes in sensory and motor function measured by functional clinical assessments.To explore the neuroplastic effects of the ABT+tSCS training programme on:Spinal circuits, assessed via transpinal-evoked potentials (TEPs) using single-pulse tSCS;Corticospinal pathways, assessed via motor-evoked potentials (MEPs) using transcranial magnetic stimulation (TMS);Somatosensory pathways, assessed via somatosensory-evoked potentials (SSEPs) using electroencephalography (EEG).

We hypothesise that ABT+tSCS training will lead to greater improvements than ABT alone in the primary and secondary clinical and neurophysiological measures.

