## Methods and analysis

### Design and setting

A single-centre, double-blind, two-arm RCT will evaluate the impact of the CIME programme (figure 1 displays the study flow). This study is part of a larger project aiming to co-develop and implement a Neuromodulation and Intensification Research Clinic for people receiving in-patient rehabilitation after a SCI.^28^ Participants will be randomly stratified and assigned to an intervention group (n=20) or control group (n=20). The intervention group will receive 20 sessions of tSCS combined with 45 min of active ABT over 6–8 weeks. The control group will follow the same treatment schedule but with sham (placebo) stimulation. Outcomes will be measured and analysed across these time points: before the training (T1), immediately after (T2) and 1 month following the end of the intervention (T3).

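### The primary group×time test names no treatment contrast and no primary time point, and the arms are then compared only through gated pairwise comparisons of cell means

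*Protocol article*

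**What the plan says.** All of the following is in the protocol article.

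- Secondary objectives states a directional hypothesis about change: "We hypothesise that ABT+tSCS training will lead to greater improvements than ABT alone".
- Trial objectives names the outcome without attaching a visit to it: "The primary outcome measure is the Upper Extremity Motor Score (UEMS) from the International Standards for Neurological Classification of Spinal Cord Injury (ISNCSCI". Design and setting and Table 2 schedule it at T1, T2 and T3 and rank no visit above another.
- Statistical analysis specifies a linear mixed model with "fixed effects for group (ABT+tSCS and ABT+sham), time (pre, post and 1-month follow-up) and the group×time interaction" and a random participant effect. It continues: "The primary effect of interest will be the group×time interaction, which will be used to determine whether changes over time differ between groups".
- The next step depends on that test: "Where a significant group×time interaction is observed, estimated marginal means will be compared using post hoc pairwise contrasts". The same sentence promises a multiplicity adjustment but names neither the method nor the set of contrasts.
- Power calculation sizes the trial on the same interaction: two groups, three time points, f=0.25, two-tailed 5%, about 34 completers for 80% power, 40 recruited.

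**The concern.** The hypothesis is that UEMS improves more with tSCS than without it. The quantity that answers this is the difference between arms in change from T1. The interaction test combines two such differences, at T2 and at T3, into one non-directional statistic. It can be significant because of an early effect that vanishes, a late effect, or a divergence between T2 and T3. With a single contrast the sign of the estimate settles the direction. With two components that may differ in size or sign, it does not.

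The stated follow-up does not repair this. A pairwise contrast of estimated marginal means is a change within one arm, a difference between arms at one visit, or a cross-arm, cross-visit pair. None is the difference in change. Both arms receive ABT on top of usual care in the subacute phase, so gains within each arm are to be expected. A significant gain in one arm and a non-significant gain in the other is then an easy but invalid conclusion. What is at stake is the headline result: which number the trial reports as the effect of tSCS, and whether a significant interaction can be traced to it.

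**Working it through.** **Inputs.** From Power calculation: 34 completers, two groups, three times, f=0.25, two-sided α=0.05. The article gives neither the correlation r between visits nor a sphericity correction. I assume unit SD at each visit, equal correlations, r=0.5, 0.7 or 0.8, and no covariates other than baseline where stated.

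**1. Degrees of freedom.** Interaction: (2−1)(3−1)=2. Error: (34−2)(3−1)=64.

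**2. The plan's own figure.** λ=f²·N·3/(1−r).
- r=0.5: λ=0.0625·34·3/0.5=12.75, power 89%; 28 participants would suffice for 80%.
- r=0.4: λ=10.63, power 82%, and 34 is the required N.
- r=0.5 with a sphericity correction of 0.75 also gives 34 (81%).

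Attrition: 34/0.85=40. So 34 is attainable under unstated assumptions, and I do not dispute it here.

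**3. What significance tells the reader.** Let δ be the arm difference at each visit. Then λ=(N/4)·Σ(δ−mean δ)²/(1−r). The patterns (0,d,d), (0,d,0) and (0,0,d) all give Σ=2d²/3, and reversing the sign of d changes nothing. At f=0.25 and r=0.4-0.5, omnibus power is 82-89% for a sustained, linear, T2-only or T3-only effect. The T1→T2 difference in change has 78-85% power for a sustained or T2-only effect, 35-41% for a linear one and 5% for a T3-only one.

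**4. Sustained effect (0,d,d) sized for 80% omnibus power.** This needs λ=10.10, so d=√(6(1−r)·10.10/34). Squared noncentralities (noncentral t, 32 df, or 31 when baseline-adjusted):
- raw T2 arm difference: d²N/4
- T1→T2 change: d²N/(8(1−r))
- baseline-adjusted T2: d²N/(4(1−r²))
- baseline-adjusted T2/T3 average: d²N/(4[(1+r)/2−r²])

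| | r=0.5 | r=0.7 | r=0.8 |
|---|---|---|---|
| d (SD) | 0.944 | 0.731 | 0.597 |
| Raw T2: squared noncentrality | 7.58 | 4.55 | 3.03 |
| Raw T2: power, unadjusted | 76% | 54% | 39% |
| Raw T2: power, Bonferroni over 3 visits | 59% | 36% | 23% |
| T1→T2 change: power (7.58 throughout) | 76% | 76% | 76% |
| Baseline-adjusted T2: power (10.10, 8.91, 8.42) | 87% | 82% | 80% |
| Baseline-adjusted T2/T3 average: power (15.15, 12.63, 11.65) | 96% | 93% | 91% |

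At r=0.4 the loss largely disappears. There d=1.034 and the raw T2 squared noncentrality is 9.09, giving 83% power unadjusted and 69% with Bonferroni over 3.

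**5. Other shapes.**
- Linear growth (0,d/2,d), omnibus power held at 80%: d=√(8(1−r)·10.10/34)=1.090, 0.844, 0.689. Baseline-adjusted T2 has 43%, 39% and 37%; T1→T2 change has 34%. The baseline-adjusted average (arm gap 0.75d) has 90%, 85% and 82%.
- Half the step 4 effect lost by T3, (0,d,d/2): omnibus power falls to 67%; the T2 contrast is unchanged.
- T2-only effect (0,d,0), with d as in step 4: the average sees half the gap, so its squared noncentralities are a quarter of those in step 4 (3.79, 3.16, 2.91) and its power is 47%, 41% and 38%.

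**The case against.** The best defence is that the treatment effect is already in the model. With T1 as reference, the two interaction coefficients are the between-arm differences in change at T2 and T3, the plan calls the interaction primary, and the power calculation tests the same thing. This stands: it would be wrong to say that the plan contains no estimate of the treatment effect, or that analysis and sample size disagree. What is missing is which component is primary, and a report of it that does not depend on the omnibus p-value.

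Several stronger readings are tempting, and the article does not support them.
- Six cell means form 15 pairs, and a reader might assume correction over all of them. The article does not list the family. Comparing arms at each visit would be three contrasts, which is why three is used above.
- A reader might infer that multiplicity is ignored. Adjustment is promised for these contrasts; only the method is open, and an analysis plan may supply it.
- A result favouring sham could be significant, but that is true of any two-sided test.
- A reader might infer that a non-significant trial will publish no effect estimate. The gate covers the post hoc contrasts, and nothing forbids reporting model coefficients with intervals.
- The number of secondary outcomes is a separate matter and adds nothing here.

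Randomisation method and blinding also says that residual imbalance, particularly in injury severity, will be adjusted for in the primary analysis. This would reduce the between-person spread in the raw comparisons, so the power figures for them may be pessimistic.

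**Conclusion.** The concern holds in this form: the article fixes a non-directional 2-df test as the primary effect, fixes no primary time point, and makes the arm comparison conditional on that test and of a kind that is not the difference in change. It is a stated decision rule, so it is not a detail left to an analysis plan that is not shown.

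The size depends on the correlation between visits, which the article does not give. Under a sustained effect with 80% omnibus power, the raw T2 comparison has 76% down to 39% power for r from 0.5 to 0.8 before any adjustment, and 59% down to 23% with three comparisons. A significant interaction that the follow-up cannot locate is then a realistic outcome. At r=0.4 the power loss is small, but the ambiguity about time and direction remains.

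The finding does not show that T2 must be the primary visit. That choice is open and carries a real trade-off. The need to name one contrast does not depend on it.

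**What to change.** Before unblinding, and preferably before recruitment opens in September 2026, amend Statistical analysis as follows.

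1. Name one 1-df between-arm UEMS contrast, adjusted for T1, as primary at two-sided 5%: either the difference at T2 or the average of T2 and T3. Make the other time point, or the separate T2 and T3 differences, key secondary.
2. Report that contrast with its 95% CI whatever the interaction p-value.
3. Replace the gated pairwise comparisons with the between-arm differences in change at T2 and T3, each with its interval. The interaction test may stay as a descriptive summary.
4. Specify baseline adjustment explicitly. It targets the same effect as the difference in change under randomisation but is not equally precise: 80-87% against 76% power in the sustained case.
5. Redo Power calculation for the chosen contrast, stating the UEMS difference, the SD and the correlation.

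The cost is wording and one recalculation; no visit or measurement changes. The statistical cost lies in the choice. A T2 contrast has about 37-43% power if the benefit grows linearly to T3. The T2/T3 average keeps 82-90% there and 91-96% if the benefit is sustained, but has only 38-47% if the benefit is confined to T2. The team should choose according to when it expects benefit and record the reason.
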